## Abstract

Background: Recent research using mobile phone interventions to address public health issues such as smoking, obesity, depression, and diabetes provides a basis for trialing a similar approach toward reducing the negative consequences of risky drinking.
Objective: This feasibility study aims to recruit drinkers between 18–34 years to a website where they will design and enter their own personal messages (repeating or one-off) to be sent to their mobile phones when they are drinking to remind them of their pre-drinking safety intentions.
Methods/Design: Participants in the treatment group will have access to the messaging function for 3 months and will be compared to a control group who will have 3 months access to a web chat site only. Data collection will occur at baseline, 3 months, and 6 months. The primary outcome is a change in unintended negative consequences from drinking at 3 months. Secondary outcomes include the acceptability of the intervention to this population, recruitment rate, participant retention, reduction in alcohol consumption, and the self-motivation discourse in participant messages.
Discussion: Existing alcohol interventions in New Zealand attempt to reduce alcohol consumption in the population, but with little effect. This study aims to target unintended negative consequences resulting from drinking by empowering the drinkers themselves to deliver safety messages during the drinking session. If proven effective, this strategy could provide a cost-effective means of reducing the public health burden associated with risky drinking.
Trial Registration: Australia and New Zealand Clinical Trials Register (ANZCTR): ACTRN12611000242921

## Introduction

New Zealand statistics about the unintended negative consequences of drinking show that young drinkers do not heed public health messages sufficiently [1]. There are numerous immediate problems caused by risky drinking, including acts of violence, driving under the influence, unintended sex, hangover, cognitive impairment, physical and verbal assault, physical accidents, relationship problems, loss of productivity, compromised mental health, and increased burden on medical and legal services [2,3]. For example, a study of the New Zealand drinking population in 2009 found that the risk of alcohol-associated accident and injury was almost 50% for those younger than 24 years compared to a 20% risk among drinkers of all ages [4].

Risky drinking can be defined generally as drinking to drunkenness [5], or quantified as more than 6 standard drinks for men (4 for women) in one drinking session [2]. In the 2007–2008 New Zealand Health Survey, 25% of respondents were identified as weekly risky drinkers. Most weekly risky drinkers were between 18–24 years (33.8% of males and 18.8% of females) followed by those between 25–34 years (16.3% of males and 12.6% of females). Young women in the 16–17 year age group were more likely to be weekly risky drinkers (16.4%) compared to young men in this same age group (9.0%) [2]. In New Zealand, the two demographic groups that engage in weekly risky drinking most frequently are between 18–24 years and 25–34 years.

Brief interventions, such as an assessment of drinking behavior and discussion about the consequences and how to change, have traditionally been left to health professionals in the public sector [6-8] or in the university campus environment [9-12]. Web-based alcohol interventions are now gaining popularity by providing information and strategies on reducing consumption and keeping safe [13-15]. Although medical and web interventions have shown some measure of success [11,16-20], particularly in the university population[12,21,22], the continuing alcohol problem among those between 18–34 years is an indication that alternate approaches are needed.

Computer- and mobile phone-based technologies have been utilized effectively in a number of health interventions, such as smoking, diabetes, obesity, and depression prevention [23-27]. The rationale behind mobile phone interventions for smoking is to send messages or relevant video to smokers’ phones when they are most likely to be tempted to smoke as a reminder of cessation intentions [24]. Similarly, a text message received while drinking could serve as a reminder of safety intentions and counter the distraction of drinking “buddies” and the drinking environment [28]. Engaging the participants in planning their own messages could add to the intervention effect due to the positive correlation between health behavior change and personally defined goals and plans [29-31]. The receipt of a planned, self-designed message sent at appropriate pre-scheduled drinking times could potentially resonate with a message recipient (whose judgment is clouded by alcohol) and result in safer behavior [32]. An additional rationale behind the drinker designing their own message (versus messages designed by a third party) is one of ontology. Researchers traditionally use focus group discussions with representatives of the target population to construct the messages used in health interventions. However, the brain of the drinker, dulled by the sedative effect of alcohol, requires a message that fully resonates within their memory [28]. It is our view that such a message can only be written by the drinkers themselves.

We have designed a feasibility study to look at whether drinkers between 18–34 years are able to fulfill their intentions of drinking safely and/or consuming less alcohol if they receive self-generated reminders of those intentions via mobile phone text messages when drinking.

The study aims to address several gaps in the alcohol brief-intervention literature, namely (1) delivery of a brief intervention by non-health professionals; (2) use of text messages as a prompt to moderate drinking and implement intentions to keep safe while drinking; (3) use of an intervention during alcohol consumption; (4) use of an intervention designed and controlled by the participants themselves; (5) how text message-prompted smoking cessation translates to the field of alcohol consumption; and (6) an insight into the self-motivation talk of drinkers.

The planned intervention puts the power and opportunity for change into the hands of those who are most at risk from the consequences of risky drinking. The intervention delivery mechanism, the mobile phone, is one that the younger drinking population is extremely comfortable using and it has been shown that they use it to transmit health information [33]. In New Zealand, 90%–94% of young people between 18–34 years own a mobile phone [34]. Changing health behaviors requires motivation, volition, and a sense of personal efficacy [30,35-37]. The process of planning the messages to be sent to their mobile phones may increase the participants’ sense of self-efficacy. Their likelihood of succeeding in their intentions could also be increased by their proactive planning of the message and scheduling of the delivery [35]. The delivery of the message during the act of drinking should cut across the physical effects of alcohol and the social environment, thereby, increasing the probability of the participant taking action on their intentions [28,38,39]. In addition, participants can respond to their own changing needs by changing the messages and message delivery times at any time. This responsiveness has been extended by a smartphone application, available for the iPhone and the Windows Phone 7, which will enable messages to be created or edited without direct access to the website. The act of planning the text delivery times and messages aims to empower the participant and add to the salience and recognition of the messages when received on their phone.

Before a full, randomized controlled trial of this intervention can be undertaken, a feasibility study needs to be run. To this end, the website and smartphone apps have been developed and tested to ensure that the website information, question format, and data collection align with the Checklist for Reporting Results of Internet E-Surveys (CHERRIES) protocol [40].

## Methods

### Objectives

The long-term objective of the feasibility study is to trial concepts needed to inform a randomized controlled trial (RCT) which will assess whether a mobile phone harm reduction strategy can reduce the number of unintended consequences resulting from a drinking session.

The primary objectives of this study are the acceptability of the intervention, a change in amount of alcohol consumed and/or a change in alcohol-related consequences, the self-talk of this population in relation to alcohol and safe drinking, and the recruitment rates and loss to follow-up over time. Such data will inform sample size calculations and the design of a subsequent RCT.

### Study Design

This is a parallel group randomized controlled trial.

### Study Population

The study population will be recruited within the Auckland Council region using media advertising, including radio and newspapers. Corporate businesses, bars, and clubs will be contacted for permission to display recruitment posters on their premises. Tertiary campuses in the study region will also be targeted through student radio, flyers, and posters, and student email lists from the campuses (where they can be sourced). Participants will be invited to sign up on the study website where they can access further information about the study. They will be asked 4 key questions to determine whether they fulfill the inclusion criteria. Those not eligible for the study will be thanked for their time, and they can sign up to receive a copy of the study results and/or notification of any subsequent trials.

Participants will not be paid for their participation, but will be entered into a monthly draw for mobile phone top-up vouchers.

### Inclusion Criteria

Participants will be between 18–34 years, have experienced at least one unintended consequence from drinking in the previous 3 months as measured by the selected Screening Test: Young Adult Alcohol Problem Severity Test (YAAPST), have access to the Internet, and own a mobile phone on any plan. Non-drinkers will not be excluded from participation as they may experience unintended consequences due to their association with drinkers. Non-drinkers may socialize with drinking friends and be the “responsible” person in the group. As such, they may want to use the text message service to remind themselves of this responsibility. We did not want to exclude non-drinkers from the study as non-drinkers can be caught up in unintended negative consequences when out with drinking friends. The Alcohol Use Disorders Identification Test alcohol consumption questions (AUDIT-C) scores will identify these non-drinkers and we will control for them in the statistical analysis.

There will be no limit to the number of participants. Recruitment will remain open for 8–10 months.

### Exclusion Criteria

Adults will be excluded if they have not experienced unintended consequences from drinking, they are outside the target age range, or they do not have their own mobile phone or access to the Internet.

### Blinding and Randomization Allocation

Participants will be allocated 2:1 to the control and intervention groups, respectively, to ensure adequate numbers for study comparison. There is evidence of a high level of attrition in the control group in Internet-based interventions. Therefore, we chose the 2:1 allocation to reduce the risk of control group dropout. The researchers will be blinded to treatment allocation. Participants fulfilling the inclusion criteria will be asked to consent to the study and answer demographic, drinking, and consequences questions before gaining on-going access to the website. Participants will be randomized to each of the two groups by computerized central randomization using stratified blocks (block size = 6). Two stratification factors will be used: gender (male/female) and age (≤ 24 years and > 24 years) to ensure balance in these key prognostic factors between the intervention and control groups. Once randomized, intervention participants will receive an appropriate email with instructions and reminders for setting up and accessing their messages.

### Study Intervention

#### Intervention Group

The study website will enable participants to create the messages they wish to have sent to their mobile phones, at the times they schedule. These messages might relate to their strategies to reduce alcohol consumption or to keep safe during and after drinking. By default, the messages will be repeated weekly based on the initial day of the week and time specified by the participant. Participants will be able to create once-only messages by entering a specific date. All messages will continue to be sent, as per the participant schedule, until they are deactivated by the participant. Participants can change their messages and schedules at any time. They will also have access to the website community pages (outlined below).

Participants who own an iPhone or Windows Phone 7 will also be able to download an application to their phone to enable them to control the messages from their mobile phone. The intervention group will have access to the intervention for six months. Figure 1 illustrates the study design.

**Figure 1 figure1:**
[figure not shown]
Study intervention and control groups.

#### Control group

Participants in this group will have access to a simple website for 3 months, where they can post messages about any topic of interest to them and participate in community discussions. The community pages will also have links to useful websites providing information on drinking safely and participants will receive a text message as these links are updated. This group will understand that they are in the control group and, after 3 months, they will receive an email or text message inviting them to access the intervention.

There will not be a limit placed on the number of messages created by the participants or on the frequency with which these messages can be sent to their mobile phones. A log of messages sent and a log of message content/schedule changes will be recorded from the website and will inform statistics on intervention usage.

### Baseline Assessments

The following data will be collected via the study website from all participants at baseline and saved directly into the Microsoft SQL Server database 2008 Enterprise R2.

#### Demographic Information

Information about gender, ethnicity, employment status, age of first drink and first drunkenness, and readiness to change drinking habits [41] will be collected.

#### Drinking History

Items 1–3 of the AUDIT-C will be used to assess alcohol intake [42]. This measure has been well validated in university students between 18–21 years [43-46], both male [47,48] and female [49]. Due to its brevity, the AUDIT-C has good utility as a computerized version [50] and when incorporated into general health risk questionnaires [51]. One limitation of the AUDIT-C is that Item 2, which provides the scale for number of alcoholic drinks consumed on a typical day, uses consumption ranges. To identify small changes in drinking habits [48] a question on typical daily consumption of each of wine/champagne, beer, spirits, alcopops/ready-to-drink beverages (RTD), and “other” alcoholic beverages will be included [52-55].

#### Other Dependencies

Question 2 of the Alcohol, Smoking and Substance Involvement Screening Test (ASSIST) will be asked to gauge other dependencies within this population. Previous research has shown a relationship between dependencies and difficulty in reducing drinking/negative consequences [56-58]. The ASSIST correlates well with the AUDIT (*r *= .82) when assessing alcohol as the substance of abuse [56].

#### Consequences Measure

The YAAPST was developed for use with American university students between 18–21 years [59], and is a sensitive measure for mild alcohol-related consequences, such as hangover, feeling sick, being late for work/school, etc [60]. The YAAPST also includes items on unintended sex and driving while drunk [61-68]. The measure can be scored as a lifetime occurrence of consequences, past year frequency, or past year severity [69]. There is good reliability for recall over a 12-month period [70]. Therefore, we expect similar reliability over a shorter period of time. This study will compare consequences at baseline, 3 months, and 6 months. To make the 3- and 6-month comparisons and avoid crossover of data, we will limit each recall period to 3 months.

One of the aspects that we will look at is whether the assessment items can be reduced and still collect the data we need. The intervention sign-on process tracks the point at which potential participants drop out before sign-up and we will be reviewing this for dropout particularly at the assessment points.

### Primary Outcomes

Primary outcomes will be collected at 3 and 6 months and include:

1. Whether the intervention engaged the interest of the participants sufficiently to make them proactive users of the mobile phone messages.

2. The acceptability of the intervention as measured by recruitment and dropout rates.

3. Safety, assessed from participant feedback and by measuring reported website misuse such as spamming others. Participant time from sign-up to last message sent until 6 months will be measured to provide an indication of the longevity of the program.

In addition, a change in unwanted consequences reported by participants in the intervention group between baseline and 6 months will provide an indication of the longevity of the intervention.

The quantitative outcomes of interest include a change in unwanted consequences and drinking. The initial question battery of AUDIT-C, YAAPST, and ASSIST will be repeated at 3 and 6 months. In addition, an open question asking the participant if they thought they had changed their drinking behavior in the previous 3 months, and if so, what changes they had made will be asked also.

The messages created by the participants will be analyzed to gain an understanding of the self-talk of this drinking population.

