### Withdrawal Criteria

There are no withdrawal criteria for this study. Participants wishing to drop out of the study can do so by returning to the website to turn off their messages. The termination of messages will be the proxy measure of dropout rate.

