### Procedure to Account for Missing Data

Analysis will be on an intention-to-treat (ITT) basis. Those lost to follow-up will be included in the data analysis and are defined as those not using the messaging function or those who fail to complete the outcomes measures at 3 months and 6 months. Missing data will be replaced by the last observation carried forward (LOCF) with no change assumed since the last message sent. If feasible, sensitivity analyses will be performed excluding participants with missing outcome data to assess the robustness of the study findings.

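### Dropout measured by turning messages off cannot register intervention participants who never create one, and conflicts with the plan's own definition of loss to follow-up

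*Protocol article*

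**What the plan says.** Under Primary Outcomes, the protocol article lists acceptability: "The acceptability of the intervention as measured by recruitment and dropout rates". The same section defines a longevity measure: "Participant time from sign-up to last message sent until 6 months will be measured". It also lists a separate outcome on use: "Whether the intervention engaged the interest of the participants sufficiently to make them proactive users of the mobile phone messages".

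Withdrawal Criteria fixes how dropout happens and how it is measured: "Participants wishing to drop out of the study can do so by returning to the website to turn off their messages", and "The termination of messages will be the proxy measure of dropout rate".

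Procedure to Account for Missing Data uses another definition. Participants lost to follow-up are "defined as those not using the messaging function or those who fail to complete the outcomes measures" at the two follow-up times, and they are to be included in an intention-to-treat analysis.

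Two features of the intervention bear on this (Intervention Group). Weekly repetition is the default: "By default, the messages will be repeated weekly based on the initial day of the week and time specified by the participant". One-off messages are also allowed: "Participants will be able to create once-only messages by entering a specific date". The Control group section adds that messages sent, and changes to their content or schedule, will be logged.

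**The concern.** Setting up a message is a step that the participant takes after randomisation, so some of those randomised to the intervention may never take it. The missing-data section anticipates such people by naming non-users. The dropout rule needs an act that they cannot perform, and the longevity measure needs a date that they do not have. One person is then lost to follow-up in one section, not a dropout in another, and without a value in a third.

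Participants who set up only one-off messages raise a related question. Once the last dated message has gone out, they receive nothing more, but they have turned nothing off. The article does not say whether a schedule that has run out is a termination.

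At stake is the reading of a feasibility result. Never setting up a message is plain evidence that the intervention was not taken up, yet the measure named for acceptability does not respond to it as dropout. Under Objectives, acceptability and loss to follow-up are among the items meant to inform the later randomised trial.

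**Working it through.** The article states no dropout, uptake or longevity figure, so there is nothing to reproduce. The check compares the definitions and then shows how the gap behaves under assumed values.

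**Definitions side by side, intervention arm only**

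| Participant | Dropout (Withdrawal Criteria) | Lost to follow-up (missing-data section) | Longevity (Primary Outcomes) |
|---|---|---|---|
| Never creates a message | Cannot occur | Yes | Undefined |
| One-off messages only, all sent | Unclear | Not clear from the wording | Defined: last send date |
| Repeating messages, turned off | Yes | Not clear from the wording | Defined: last send date |

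The first row is the conflict. In the second row only attrition status is in doubt, because a one-off message has a send date that the log records.

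**Size of the dropout gap**

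Assumed inputs (none is in the article):
- p, the share of the intervention arm that never creates a message
- d, the share of message creators who turn their messages off

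Formulas:
- Never-users counted: p + (1-p)d
- Never-users kept in the denominator as retained: (1-p)d. The gap is p.
- Never-users left out altogether: d. The gap is p + (1-p)d - d = p(1-d).

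| p | d | Counted | Retained (gap) | Left out (gap) |
|---|---|---|---|---|
| 10% | 20% | 28% | 18% (10 points) | 20% (8 points) |
| 20% | 20% | 36% | 16% (20 points) | 20% (16 points) |
| 40% | 20% | 52% | 12% (40 points) | 20% (32 points) |
| 10% | 40% | 46% | 36% (10 points) | 40% (6 points) |
| 20% | 40% | 52% | 32% (20 points) | 40% (12 points) |
| 40% | 40% | 64% | 24% (40 points) | 40% (24 points) |

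Whenever p is above zero and d is below 100%, both treatments give a lower rate than counting never-users. At p = 0 there is no gap.

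**Once-only users, dropout.** Assume that 20% of users set up only one-off messages and that 30% of the others turn their messages off. Dropout is 0.80 × 30% = 24% if only an act of turning off counts, and 24% + 20% = 44% if a schedule that has run out also counts.

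**Longevity.** Assume a mean of 18 weeks to the last message among creators. If never-users are omitted, the reported mean stays at 18.0 weeks. If they are scored 0 it is (1-p) × 18, which is 16.2, 14.4 and 10.8 weeks at p = 10%, 20% and 40%. The overstatement therefore depends on omission. Once-only users pull the mean down when scored: with 20% of them at week 4 and the rest at 18 weeks, it is 0.80 × 18 + 0.20 × 4 = 15.2 weeks.

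**The case against.** The strongest reply is that non-uptake and dropout are different quantities and that the plan already has a place for non-uptake. The outcome on proactive use fails for anyone who never creates a message, and the log identifies them. This stands in part: non-uptake need not go unreported, and a reader should not infer that the later trial will receive inflated uptake figures. It does not repair the dropout rate, which is the attrition measure named for acceptability.

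A second reply is that scoring rules and denominators usually belong in an analysis plan or full protocol, neither of which is shown, and that the article states no threshold for dropout or longevity. That would answer a mere omission. Here the article states a rule for dropout and a different rule for loss to follow-up, and they disagree about the same people.

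Three stronger readings are tempting, and the article does not support them:
- A reader might infer that the plan is bound to overstate longevity. The article does not say that never-users are omitted. The missing-data section includes those lost to follow-up in the analysis, although it sets no longevity score for them.
- A reader might infer that once-only users cannot be scored for longevity. They can, by their last send date.
- A reader might infer that reported dropout must fall as more people never start. That is so only if never-users stay in the denominator as retained. If they are left out, the rate stays at d.

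**Conclusion.** The point holds for dropout. As the rule is worded, intervention participants who never create a message cannot register as dropouts, although the missing-data section treats them as lost. The rate that measures acceptability is therefore understated relative to that section, by p or by p(1-d) according to how never-users are handled. The direction follows from the wording. The size does not, since every value of p and d used here is assumed.

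For once-only users the finding is narrower: their dropout status after the last message is unclear. For longevity it is conditional: the measure is undefined for never-users and biased upward only if they are left out.

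The conclusion concerns the intervention arm. It does not cover repeating messages left running by someone who has lost interest, which is a separate matter.

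**What to change.** Reconcile Primary Outcomes, Withdrawal Criteria and Procedure to Account for Missing Data so that they share one description of attrition in the intervention arm:

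- Use everyone randomised to the intervention as the denominator.
- From the message log, classify each participant as never started, started then stopped, or still active at 6 months, and report the three shares, which sum to 100%. Place a once-only schedule that has run out under started then stopped, with no act of turning off required.
- Report longevity with never-starters scored 0 and, beside it, longevity among starters, so that uptake and persistence can be read separately.

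The cost is wording in these sections, and the log already planned supplies the data. The downside is that reported non-use will be higher and reported longevity shorter than under a reading that omits never-starters.

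### Weekly messages repeat until switched off, so time to last message sent and message termination record failure to deactivate, and flatter longevity and dropout

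*Protocol article*

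**What the plan says.** All references are to the protocol article.

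- **Intervention Group, how messages run:** "By default, the messages will be repeated weekly based on the initial day of the week and time specified by the participant". And: "All messages will continue to be sent, as per the participant schedule, until they are deactivated by the participant". One-off messages are the alternative: "Participants will be able to create once-only messages by entering a specific date".
- **Primary Outcomes, longevity:** "Participant time from sign-up to last message sent until 6 months will be measured to provide an indication of the longevity of the program".
- **Primary Outcomes, acceptability:** "The acceptability of the intervention as measured by recruitment and dropout rates".
- **Withdrawal Criteria, how one leaves:** "Participants wishing to drop out of the study can do so by returning to the website to turn off their messages". And: "The termination of messages will be the proxy measure of dropout rate".
- **Control group section, usage data:** "A log of messages sent and a log of message content/schedule changes will be recorded from the website". Both logs are to feed the usage statistics.
- **Procedure to Account for Missing Data:** a separate definition treats as lost to follow-up anyone who does not use the messaging or does not complete the outcome measures at 3 and 6 months.

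The duration of access is given as six months in the Intervention Group section and as 3 months in the Abstract.

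**The concern.** Longevity is timed to the last message the system sends, and dropout is recorded when the participant switches messages off. With a weekly repeat as the default, sending needs no action after set-up, whereas stopping it needs a return visit. A participant who has lost interest has little reason to make that visit. Such a person then accrues near-maximum longevity and adds nothing to the dropout rate.

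The measure can also rank participants the wrong way round. Someone who writes a fresh one-off message each week for 12 weeks and then stops scores about 12 weeks. Someone who sets one repeat in the first week and never returns scores about 26.

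Acceptability and longevity are listed among the primary outcomes of a study whose purpose is to inform a full trial. If the definitions are followed as written, the error in both runs towards a more acceptable and more durable intervention.

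**Working it through.** The article gives no figure for longevity or dropout, so there is nothing to reproduce. The check applies its own rules to one participant.

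**Inputs**
- Default repeat every 7 days, sent until deactivated (Intervention Group).
- Longevity is time to the last send, capped at 6 months (Primary Outcomes).
- Assumptions: 6 months = 182 days; first send on day d, with d from 0 to 13 after sign-up; message never edited or deactivated.

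**1. Longevity of one untouched message**

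Sends fall on days d, d + 7, d + 14, and so on, up to day 182.
- d = 0: last send on day 0 + 7 × 26 = 182, with 27 sends; 182/182 = 100% of the cap.
- d = 1: last send on day 1 + 7 × 25 = 176, with 26 sends; 176/182 = 96.7%.
- d = 13: last send on day 13 + 7 × 24 = 181, with 25 sends; 181/182 = 99.5%.

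Over all d from 0 to 13, the last send falls on days 176 to 182 (96.7% to 100% of the cap), with 25 to 27 sends. Taking 183 days gives the same picture.

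**2. Comparison with one-off messages**
- A single one-off message on day 7: 7/182 = 3.8%.
- One new one-off message each week for 12 weeks, the last on day 84: 84/182 = 46.2%.

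The second participant acted 12 times and scores less than half of what the untouched repeat scores.

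**3. If access lasts 3 months (Abstract)**

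With 91 days, the last send falls on days 85 to 91 (85/91 = 93.4% to 100% of that period), with 12 to 14 sends. The artefact is the same but stops at 3 months, so full 6-month longevity could not be reached.

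**4. Status of the same participant under the two attrition rules**

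| Untouched repeat, and the participant | Withdrawal Criteria (termination) | Missing-data section |
|---|---|---|
| completes the questionnaires | not a dropout | not lost |
| does not complete them | not a dropout | lost to follow-up |

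The second row is a direct conflict: one person is retained under one rule and lost under the other.

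**5. Possible size (assumed shares only)**

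Suppose 10% deactivate, and a further share s lose interest but leave a repeat running. Termination-based dropout stays at 10%, while disengagement is 10% + s: 20%, 40% or 60% for s = 10%, 30% or 50%.

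Suppose a share p stops engaging at week w without deactivating. Mean longevity is then overstated by about p × (26 − w) weeks:
- p = 20%, w = 13: 0.2 × 13 = 2.6 weeks
- p = 40%, w = 4: 0.4 × 22 = 8.8 weeks
- p = 60%, w = 4: 0.6 × 22 = 13.2 weeks

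Nothing in the article fixes s, p or w. If everyone who loses interest deactivates, the overstatement is zero.

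**The case against.** The best defence is that setting a reminder once and leaving it to run is how the intervention is meant to work. Unwanted texts on one's own phone are a nuisance, so not switching them off says something. The article offers its measures modestly, as an indication and a proxy. All of this stands as far as it goes: delivery time is a legitimate quantity, and an unedited repeat is not proof of abandonment. But delivery time cannot separate a contented user from one who has stopped paying attention, and the plan reads it as longevity.

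Three stronger readings are tempting and are not supported.

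- **That such a participant would be reported as a proactive user.** The first primary outcome states no criterion based on sends, and the planned change log would show no activity after set-up.
- **That such a participant is never counted as lost.** This is true only of the termination proxy. The missing-data section captures anyone who does not complete the questionnaires. The Objectives name recruitment and loss to follow-up as inputs to the later trial, so it does not follow that its attrition allowance must be wrong.
- **That the bias has a known size.** The figures in step 5 rest wholly on assumed shares.

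It is also fair to say that the between-group comparison of drinking and consequences scores does not use the longevity measure, and that the Abstract lists acceptability and retention as secondary outcomes.

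**Conclusion.** The point holds in a limited form. As defined, time to last send and message termination largely reflect whether a participant switched messages off. One untouched default message scores 96.7% to 100% of the 6-month cap and is not a dropout under the Withdrawal Criteria. This rests on the default repeat being used, a first send within two weeks of sign-up, and six-month access as in Methods; the conflict with the Abstract's 3 months must be reconciled. It does not apply to participants who use only one-off messages.

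The direction is clear: for anyone who disengages without deactivating, longevity is overstated and dropout understated. The amount cannot be determined from the article. The termination proxy also conflicts with the definition of loss to follow-up, so the acceptability outcome could be reported two ways from the same data.

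**What to change.** **Primary Outcomes.** Make time from sign-up to the last participant-initiated action (a message created, edited, rescheduled or deactivated) the engagement and longevity measure, taken from the change log described in the Control group section. Report time to last send beside it as an upper bound. Confirm that changes made through the phone application reach the same log.

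**Withdrawal Criteria.** Base the dropout rate on non-completion of the 3- and 6-month questionnaires, in line with the missing-data section. Report message termination separately, and do not count a still-running repeat as retention by itself.

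**Cost.** This is a change of wording, since the logs and questionnaires are already planned. Longevity and retention figures will look less favourable. Time to last action is a lower bound for users content to leave a repeat unedited, which is why both bounds should be shown. A minimum number of actions per period would misclass these users and is not needed. An optional follow-up item asking whether the messages are still wanted would separate contented from disengaged users, at the price of one more question.
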